## Introduction

1

Chemotherapy-induced nausea and vomiting (CINV) is among the most common and distressing side effects of chemotherapy.^[1]^ It has been shown to significantly affect the quality of life (QoL) and daily function of patients receiving chemotherapy.^[2]^ Moreover, CINV, as a prognostic factor for overall survival, is so severe in some cases that it interrupts the treatment of primary cancer and increases the risk of disease progression,^[3,4]^ which result in treatment-outcome reduction.^[5]^

Cisplatin, which is a cornerstone of chemotherapy for the treatment of multiple cancers, is a highly emetogenic chemotherapy drug.^[6]^ Over 90% cancer patients will vomit within the first 24 hours after the administration of cisplatin-based chemotherapy unless antiemetic drugs are used.^[7]^ Even with the guideline-recommended antiemetic drugs, cisplatin-induced vomiting is controlled in only 60% of patients; therefore, considerable numbers of patients still experience nausea.^[8]^

Although the mechanisms underlying CINV are not clear enough,^[9]^ to date, commonly prescribed medicines,^[10]^ for nausea and vomiting are: 5-hydroxytryptamine-3 serotonin receptor antagonists (5-HT3RA), Neurokinin1 receptor antagonists (NK-1RA), and corticosteroid.^[11]^ However, for all its prominence in CINV management, these drugs are subject to considerably economic burden and side effects, namely insomnia, headaches, dizziness, and constipation.^[12]^ Thus, additional treatments are urgently needed to effectively manage and ameliorate chemotherapy-induced nausea and vomiting (CINV), without those defects in the wake of antiemetic drugs.

An increasing body of evidence points that electroacupuncture (EA) may provide modest benefits in the treatment of CINV.^[13]^ However, the spread of it is surprisingly slow, and EA is still judged as a highly suggestive but not conclusive treatment.^[14–17]^ For certain patients, they are reluctant to accept EA treatment for their intolerance to needling. The problems and limits of EA center on how it manipulate. Thus, auricular acupuncture (AA) might be a sound treatment to feather all patients’ needs for convenience and comfort. Compared with a pile of studies conducted the access to the effectiveness of EA against CINV, the role of AA has received less attention,^[18]^ and the literatures on AA are limited in number with uncertain quality.

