To our knowledge, there are no randomized controlled trails comparing the effect and safety of AA versus EA in cancer patients who experience CINV. Therefore, the present study is designed to determine the efficacy and safety of AA versus EA in ameliorating CINV among patients receiving cisplatin-based regimens.

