### Sample size calculation

2.6

Using the frequency of onset as the primary outcome measurement, NQuery Advisor software (version 4.0, Statistical Solutions, Ireland) was used to calculate the appropriate sample size. Based on literature research, the sample size was estimated according to the calculation formula of non-inferiority test. α = 0.025, β = 0.2, non-inferiority margin δ = 15%, ε is the actual difference among groups. One-way test was performed, and the sample size was calculated to show that 103 samples are needed in this study. One hundred eighteen cases were needed in the 3 groups, assuming a 10% non-adherence to treatment and a 5% loss to follow-up. In this study, a total of 120 cases were selected from 3 groups, 40 cases in each group.

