### Statistical analysis

2.8

All continuous data will be expressed as mean ± standard deviation. For these data, a *t* test will be applied to compare normally distributed data between the 2 groups, while the Wilcoxon rank sum test applied for non-normally distributed data. Categorical variables will be presented as frequency and percentage and analyzed using the chi square (χ2) test or the Mann–Whitney *U* test where appropriate. Values of *P* < .05 (2-tailed) will be considered statistically significant. All the efficacy and safety analyses will be performed using the intent-to-treat population. All statistical analyses will be performed using the Statistical Package for the Social Sciences (version 13.0; SPSS; Chicago, IL). A third person performed blinded estimation and statistics of the curative effect.

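### Safety is to be analysed only by assigned arm, so patients never needled, or given the other treatment, can lower or misplace needle-related event rates

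*Protocol article*

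**What the plan says.** Section 2.8 (Statistical analysis) fixes the analysis population in one sentence: "All the efficacy and safety analyses will be performed using the intent-to-treat population". It makes no exception for safety and names no set defined by treatment received.

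The Introduction gives the purpose of the trial as to "determine the efficacy and safety of AA versus EA in ameliorating CINV", so safety of the two needle treatments is part of the aim. Section 2.5.3 records every adverse event whatever the intervention, and then grades its relation to the intervention.

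Section 2.6 (Sample size calculation) arrives at its total by "assuming a 10% non-adherence to treatment and a 5% loss to follow-up". It also says that "the sample size was estimated according to the calculation formula of non-inferiority test", with "α = 0.025, β = 0.2, non-inferiority margin δ = 15" percent. Section 2.8, by contrast, names only two-sided difference tests at P < .05.

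**The concern.** Intent-to-treat keeps each patient in the arm to which randomisation assigned them. For efficacy that protects the comparison. For safety it can work against the question, which is what happens to people who are actually needled.

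- A patient assigned to AA or EA who never receives a needle cannot have a needle-related event, yet counts in the denominator of that arm.
- A patient who receives the other needle treatment has any event it causes counted against the treatment they did not get.

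Such patients are foreseeable. The Introduction says that some patients are unwilling to have EA because they do not tolerate needling, and section 2.7 says that participants cannot be blinded, so they will know their allocation. If refusals are more common in EA than in AA, the dilution is unequal and the AA-versus-EA safety comparison is itself distorted.

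This is a stated rule and not an omission. A separate analysis plan that used a treatment-received safety set would contradict the sentence in section 2.8.

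**Working it through.** **Inputs from the protocol article.** 40 patients per group; 10% non-adherence and 5% loss to follow-up (2.6); needling on 4 days per cycle over three cycles (2.4 and Table 1), that is 4 × 3 = 12 sessions; Group C receives no acupuncture (2.4).

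**The plan's own figure.** 103 × (1 + 0.10 + 0.05) = 103 × 1.15 = 118.45, which gives the stated 118, raised to 120. So the 10% is a working assumption of the plan. The article does not say whether it means patients never treated or patients who miss some sessions.

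**Dilution of needle-related rates.** Let *u* be the fraction of a needle arm that is never needled and *r* the needle-related event rate among those needled. The intent-to-treat rate is (1 − *u*) × *r*, so the relative understatement is exactly *u*. The values of *r* are assumptions, since the article gives none.

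| *u* | needled, of 40 | *r* = 10% appears as | *r* = 20% appears as | *r* = 30% appears as |
|---|---|---|---|---|
| 0 | 40 | 10% | 20% | 30% |
| 5% | 38 | 9.5% | 19% | 28.5% |
| 10% | 36 | 9% | 18% | 27% |

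The last row is the upper end for the plan's 10%: every non-adherent patient receives no needle at all. If all of them miss only some of the 12 sessions, *u* = 0 and the first row applies.

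**Upper limit when no event is seen.** The exact one-sided 95% limit is 1 − 0.05^(1/n).

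- n = 40: 1 − 0.05^(1/40) = 7.2%
- n = 36: 1 − 0.05^(1/36) = 8.0%

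**Misattribution.** With 40 per arm, one event counted in the wrong arm adds 1/40 = 2.5 percentage points to that arm. The article gives no basis for how often this would happen.

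**Secondary: the non-inferiority aim of 2.6.** Suppose a non-inferiority test were run on intent-to-treat alone. Assume 40 per arm, a true deficit equal to the 15-point margin, and 10% of patients in each arm non-adherent with the same response in both arms.

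- Intent-to-treat deficit: 0.90 × 15 = 13.5 points, a shift of 1.5 points in favour of the claim.
- Standard error: √(2p(1 − p)/40). At p = 0.5 this is 0.112; at p = 0.4 or 0.6 it is 0.110.
- Error: P(Z > 1.96 − 0.015/SE). At p = 0.5 this is P(Z > 1.83), about 0.034; at p = 0.4 or 0.6 it is also about 0.034, against a nominal 0.025.

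**The case against.** The strongest objection is that non-adherence is not the same as never being needled. With about 12 sessions per patient, and with Group A patients also asked to press the points three times a day, most non-adherent patients may well be needled at least once. They would stay in a treatment-received set, and the denominators would hardly change. This stands: the documents do not say how many patients, if any, will go un-needled. A reader might infer that event rates in both needle arms will be understated by a tenth. The documents support that only as an upper figure.

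Second, the multiplier applies only to events caused by needling. Section 2.5.3 collects all adverse events, and un-needled patients on cisplatin will have events too, so all-cause rates are not scaled by 0.90. This also stands.

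Third, a reader might infer that intent-to-treat raises this trial's false non-inferiority rate above 2.5%. The documents do not support that as it stands. Section 2.8 plans only two-sided difference tests, for which pulling the arms together is ordinarily conservative. Section 2.6 does not name AA versus EA as the non-inferiority contrast and speaks only of groups in general ("ε is the actual difference among groups"). The pull towards no difference also needs similar non-adherence in both arms; unequal non-adherence could act either way. Nor should the 5% loss to follow-up be added to the 10%: lost patients have no outcome, and their effect depends on how missing data are handled.

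Fourth, the effect is small beside other problems. At 40 per arm, with 50% incidence in both arms, power to show non-inferiority within 15 points is only about 27%, and the mismatch between 2.6 and 2.8 is a larger and separate matter. That is fair, and it limits the weight of the non-inferiority part. It does not touch the safety part, which rests on the wording of 2.8 alone.

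**Conclusion.** The safety point holds. Section 2.8 rules out analysing safety by treatment received, although safety of AA versus EA is an aim and non-adherence is expected. Needle-related event rates can be understated, by a relative amount equal to the never-needled fraction: between nothing and about one tenth on the plan's own 10%, with the upper end reached only if every non-adherent patient receives no needle. Misattribution is possible, but its size cannot be judged from the article. The effect is modest, and the rule should be changed before analysis because the change is nearly free.

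The non-inferiority point is secondary and conditional. It applies only if the aim in 2.6 is kept and a matching test is added to 2.8. An error of about 0.034 instead of 0.025 then rests on 10% non-adherence that is alike in both arms, 40 per arm and assumed incidences of 40–60%.

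**What to change.** In section 2.8, restrict the intent-to-treat sentence to efficacy. Add that safety will be analysed by treatment actually received: patients with at least one needling session form the AA or EA safety set according to what they received, and Group C is the un-needled comparator.

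If the non-inferiority aim of 2.6 is kept and a non-inferiority test is written into 2.8, add that a per-protocol analysis will be reported beside the intent-to-treat one.

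The cost is one or two sentences and one extra set of tables, with no new data and no change to treatment. The downside is slightly smaller safety denominators and loss of the strict randomised comparison for safety.

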## Discussion

3

Acupoint therapies, including EA and AA, have the characteristics of higher acceptability, limit side effects, and inexpensiveness.^[22]^ And yet, the fast growing piles of studies, especially low to moderate evidences,^[23,24]^ do not give us any firm grasp of reasoned acupuncture regimen for preventing CINV. The shortage of the studies which compare different acupuncture therapies cause that clinicians are unable to determine the therapeutic values of them, which is unavailable for selecting the most appropriate treatment.^[25]^ Rather, this is not the whole story. To our best knowledge, there is no single regimen could completely blocking CINV.^[26]^ Therefore, relative studies should focus on all categories of CINV. Unfortunately, most previous researches paid more attention on acute CINV, while delayed CINV is a more common, severe and hard-to-cure subtype.^[27]^ To meet the clinic needs, we design this trail to compare the effectiveness and safety of EA and AA for CINV induced by cisplatin-based regimens in a strictly devised situation, and develop a standardized alternative therapy for medical staff.

To minimize the bias, stratified block randomization and blinding will be applied, and participants will be avoided any communication with others farthest, shaped by separate treatment time and diagnosis rooms.

Despite its strengths, this study has, nevertheless, an obvious limitation. It is a single-center study, which may limit its generalizability so a future multiple-center large-sample size study will be needed. However, the results of this trail will provide more evidence and will help medical staffs make a better choice for patients.
